# High-concentrated platelet-rich plasma (PRP) versus placebo in osteoarthritis in the thumb base: study protocol for an assessor-blinded randomized controlled trial

**DOI:** 10.1186/s13063-024-08636-2

**Published:** 2024-11-26

**Keywords:** Thumb, Osteoarthritis, Platelet-rich plasma, Randomized controlled trial, Placebo, Carpometacarpal joint

## Abstract

**Background:**

Osteoarthritis in the thumb base (trapeziometacarpal joint, CMC-1 joint) is prevalent, particularly among middle-aged and elderly women, causing significant disability. Conservative treatments, including steroid injections, have been questioned for their efficacy, prompting exploration into alternative therapies such as platelet-rich plasma (PRP) injections. This randomized, double-blinded, controlled trial aims to evaluate the effectiveness of high-concentration PRP (platelet-rich plasma) injection compared to saline (placebo) in reducing pain and disability in patients with thumb base osteoarthritis.

**Methods:**

Patients meeting inclusion criteria will be randomized and blinded, with injections administered under sterile conditions and radiological guidance.

With a planned sample size of 90 patients recruited from the Department of Hand Surgery at Södersjukhuset, Stockholm, the study will assess pain relief and functional improvement at 3, 6, and 12 months post-injection. The primary outcome measure is pain on load (numerical rating scale) at 6 months, with secondary outcomes including patient-reported outcomes, key pinch, grip strength, abduction of the thumb, and time to intervention within 1 year.

Statistical analyses will employ non-parametric tests, chi-square tests, and generalized estimating equations to compare outcomes between the PRP and placebo groups.

**Discussion:**

The study aims to provide evidence regarding the efficacy of high-concentration PRP injections for thumb base osteoarthritis. If PRP proves superior to saline in reducing pain and improving function, it could offer a promising alternative treatment. Conversely, if PRP does not demonstrate significant benefits over placebo, its use for this condition is not justified. This study seeks to address the current gap in evidence regarding the efficacy of PRP injections for thumb base osteoarthritis.

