### Outcome

The primary outcome is as follows: change of pain on load (numerical rating scale (NRS) 0–100) in the thumb from before the first injection to 6 months after.

The secondary outcomes are as follows:Change in PROMs (Patient-Reported Outcome Measures) from pre-injection to 3, 6, and 12 months, including Patient-Rated Wrist/Hand Evaluation (PRWHE) score [23], Nelson score [24], and HQ-8 score [25]Objective physical variables: key pinch and three-finger pinch strength measured by using the Saehan Medical® mechanical pinch gauges SH5010 (the mean value of three consecutive measurements is used), radial and palmar abduction of the first metacarpal [26], thumb opposition [27] (Kapandji score). All measurements are performed according to the manual for measuring motion and strength in the Swedish national quality registry HAKIR [26]Time for the patient to experience the need for an intervention in the form of renewed injection, steroid injection, or surgery within 1 year after injection. Any adverse events, complications, and failures (defined as lack of improvement or deterioration of pain) during the study period will be recorded

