### Sample size

To show a difference of 20 points (out of 100), representing the minimal clinical difference [28], in pain on load NRS score between PRP and saline injection (SD 30) (3) after 6 months, 37 patients are required in each treatment arm. The power will be 80% (*p* < 0.05). To account for non-parametric outcomes and loss to follow-up, we aim to include 90 patients in total, 45 in each treatment arm.

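### The abstract draws a negative practice conclusion from non-significance alone, although at the plan's own inputs some non-significant results would not exclude its 20-point minimal clinical difference

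*Protocol article*

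**What the plan says.** The discussion part of the abstract sets out two readings of the result. If PRP is superior, it could be a promising alternative. Otherwise: "Conversely, if PRP does not demonstrate significant benefits over placebo, its use for this condition is not justified".

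The primary outcome (Methods, Outcome) is "change of pain on load (numerical rating scale (NRS) 0–100) in the thumb from before the first injection to 6 months after". The Sample size section sets the target: "To show a difference of 20 points (out of 100), representing the minimal clinical difference", "in pain on load NRS score between PRP and saline injection (SD 30) (3) after 6 months". It states that "37 patients are required in each treatment arm" for 80% power at the 5% level. It then adds a margin: "To account for non-parametric outcomes and loss to follow-up", "we aim to include 90 patients in total, 45 in each treatment arm". No loss rate is given.

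The Statistical analyses section names the rank sum test for change in patient-reported outcomes and a generalized estimating equations (GEE) model adjusted for pain catastrophizing, gender and Eaton class. The article sets no equivalence or futility margin. The main Discussion neither repeats nor qualifies the abstract's sentence; the limits it states are the short follow-up, the single centre and the unknown platelet concentration per patient.

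**The concern.** The sentence goes from lack of significance to a statement about practice without asking what the data exclude. A superiority trial can miss significance in two different ways. The interval may lie wholly below the difference that matters, which is informative against PRP. Or it may contain both zero and that difference, which settles nothing. The sentence treats the two alike.

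At stake is how the result is reported. The abstract presents the trial as filling an evidence gap, and an inconclusive result could be published as a reason not to use PRP.

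**Working it through.** **Inputs.** Difference 20 points, SD 30, power 80%, alpha 0.05, 37 per arm required and 45 per arm planned (all from Sample size). Because no loss rate is stated, I take 37 to 45 analysable per arm as an assumed range, that is 1 − 37/45 = 17.8% down to 0% loss.

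**Reproducing the plan's figure.** For a two-sided comparison of two means, the normal approximation gives 2 × (1.96 + 0.842)² × 30² / 20² = 35.3, so 36 per arm. The t-test solution is 36.3, so 37 per arm, which matches. A one-sided test would need only 28, so the design is two-sided.

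**Precision.** Half-width h = t(0.975, 2n − 2) × SD × √(2/n).

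- n = 37: SE = 30 × √(2/37) = 6.97; h = 1.993 × 6.97 = 13.90.
- n = 45: SE = 30 × √(2/45) = 6.32; h = 1.987 × 6.32 = 12.57.

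**Ambiguous band.** Let d be the observed benefit of PRP over saline. The result is non-significant if |d| < h, and the CI fails to exclude 20 if d + h ≥ 20. Both hold for 20 − h ≤ d < h:

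- n = 37: 6.1 to 13.9 points.
- n = 45: 7.4 to 12.6 points.

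**How often.** With a normal sampling distribution for d (SD 30):

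| True benefit | Non-significant, 37 / 45 per arm | Non-significant and CI includes 20 | Share of non-significant results that include 20 |
|---|---|---|---|
| 0 | 95% / 95% | 17% / 10% | 18% / 10% |
| 10 | 71% / 66% | 42% / 32% | 60% / 48% |
| 20 | 19% / 12% | 17% / 10% | 88% / 81% |

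For a true benefit of 20 and n = 45, for example: (12.57 − 20)/6.32 = −1.18, which gives a probability of 0.12.

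**Sensitivity to the SD.** The band exists only if h > 10, that is if SD > 10 / (t × √(2/n)): above about 22 for 37 per arm and about 24 for 45 per arm.

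| SD | Band, 37 per arm | Band, 45 per arm |
|---|---|---|
| 20 | none | none |
| 25 | 8.4–11.6 | 9.5–10.5 |
| 30 | 6.1–13.9 | 7.4–12.6 |
| 35 | 3.8–16.2 | 5.3–14.7 |

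**When the sentence would be safe.** At SD 30, every non-significant result excludes 20 only if h ≤ 10, which needs about 71 per arm (70 by the normal approximation) against the planned 45.

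**The case against.** **It is closing rationale in an abstract, not a decision rule.** The sections on outcomes, sample size and analysis contain no rule for a null result. This stands as a limit on severity. It does not remove the point, because no other text says how a null result will be read.

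**The word significant may not be meant statistically.** Elsewhere the article uses it in its everyday sense, of disability and of patients' problems. That reading is possible. In a sentence about demonstrating benefit over placebo in a trial planned on a significance test, the statistical reading is the more natural one, and a rewording would settle it.

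**Saying that use is not justified is not saying that PRP does not work.** This stands. A reader might infer that the protocol treats non-significance as proof of no benefit, but the sentence does not say so. It can be read as placing the burden of proof on the new injection, and on that view an inconclusive trial also fails to justify use. What remains is that the sentence gives an inconclusive trial and an informative null trial the same conclusion.

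**The size depends on unknowns.** This stands too. If PRP has no effect, only 10–18% of non-significant results stay compatible with 20 points. The larger shares at a true benefit of 10 points concern an effect half the plan's own minimal clinical difference, where a negative practice conclusion would not be wrong by the plan's standard, so the point does not rest on them. The 12–19% at a true benefit of 20 is ordinary type II error, already disclosed as 80% power. The SD of 30 is given for the score, whereas the primary outcome is a change whose SD is not stated, and covariate adjustment may reduce it.

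**A CI rule needs an estimator.** This is correct: the rank sum test does not by itself give an interval for a mean difference. The fix therefore has to name one.

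**Conclusion.** The point holds as a fault of stated interpretation. At the protocol's own inputs, a band of non-significant results (6.1–13.9 points with 37 per arm, 7.4–12.6 with 45) does not exclude the 20-point difference the trial was planned to detect, and the abstract would read these as a reason not to use PRP. With a true 20-point benefit, that negative reading follows in 19% to 12% of trials.

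This rests on an SD of 30 for the change score, a two-sided 5% level and 37 to 45 analysable per arm. Below an SD of about 22 (37 per arm) or 24 (45 per arm), every non-significant result excludes 20 points and the practical problem is gone.

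A reader might also infer that the trial is too small. The documents do not support that: 37 per arm reproduces, and 45 allows for loss. The figure of 71 per arm shows only what the abstract's sentence would require, and is not a target for the trial. The defect is confined to one sentence, so it is modest, but it is worth correcting before the data are analysed.

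**What to change.** Replace the sentence with a reading based on the 95% CI of the between-group difference in change of pain on load at 6 months, and name the estimator. Two candidates fit the planned analyses: the adjusted mean difference at 6 months from the GEE model, or a Hodges–Lehmann interval reported with the rank sum test.

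With positive values favouring PRP, for a result that does not show superiority:

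- If the CI lies wholly below 20 points, state that a benefit of the minimal clinical size is excluded for the single-injection preparation tested.
- If the CI includes both 0 and 20, report the result as inconclusive, with benefit unproven.

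Applying this wording only when superiority is not shown avoids a clash if the SD proves small. At SD 20 and 45 per arm, h is 8.4, so an observed benefit of 10 points would be significant and still have an upper limit below 20. That result should be reported as a benefit smaller than the minimal clinical difference.

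The change costs a reworded sentence and the naming of one estimator. Sample size, conduct, primary outcome and tests are untouched. The downside is a narrower negative claim.

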**Trial registration:**

The study has been approved by the Swedish Ethical Review Authority (2023–06860-01 and 2024–01238-02) and is registered on ClinicalTrials.gov (NCT06193499) 2024–01-04.

**Supplementary Information:**

The online version contains supplementary material available at 10.1186/s13063-024-08636-2.

## Background

Osteoarthritis in the thumb base (trapeziometacarpal joint, CMC-1 joint) is very common, especially from middle age and in women [1, 2] and may cause significant disability [3].

Conservative treatment includes patient education in joint protection, splints, exercises, analgesics, and intra-articular steroid injections [4–7]. The effect of steroid injections in thumb base osteoarthritis has been questioned [8], particularly due to the short effect [9] and concern that intra-articular steroids may degenerate articular cartilage in osteoarthritis [10].

Intra-articular injection of platelet-rich plasma (PRP) has arisen as an alternative treatment for osteoarthritis. PRP is derived by centrifugation of autologous blood to separate the plasma containing high platelet concentrations. It is prepared and administrated in the outpatient clinic. PRP is a cocktail of platelets, growth factors, and inflammatory mediators that may be effective for cartilage repair [11]. In addition, the fibrinogen in PRP may be activated to form a fibrin matrix to fill cartilage lesions [12].

PRP has demonstrated effective pain relief and functional improvement compared to hyaluronic acid or saline without increased risk of adverse events in the treatment of knee osteoarthritis [13]. In patients with knee osteoarthritis, PRP is reported to decrease pain more and for a longer duration than steroid injections [14]. There is little data on the effect of PRP on hand osteoarthritis. In a small study of 33 patients, PRP had reportedly better long-standing pain reduction in thumb-base osteoarthritis than intra-articular steroid injections [15]. In another small RCT with short-term follow-up, the effect of PRP compared to corticosteroid and hyaluronic acid showed a positive effect of PRP only at 4 weeks; at 12 weeks, the effect had ceased [16]. Other studies on PRP in the thumb base are retrospective and/or include other joints and therefore have a low level of evidence, and results are contradictory [17, 18]. A recently published meta-analysis concluded the need for a good placebo controlled RCT on PRP in thumb base osteoarthritis [19].

Studies have shown that the concentration of platelets is essential for the effect of PRP in knee osteoarthritis, with higher concentrations providing better chondro-protection and alleviation of symptoms [20], and that repeated injections can result in a better effect [21]. Using a double-spin technique in producing the PRP, the concentration of platelets is even higher than in the single-spin PRP previously most commonly used in intra-articular injections. The thumb base joint is much smaller than the knee, and only a small amount of PRP (< 1 ml) can be injected. Hence, high-concentration PRP may be beneficial in this small joint.

This study aims to evaluate whether a single high-concentration PRP injection decreases pain and disability in patients with thumb base osteoarthritis in the short term and compare the effect to placebo.

### Research questions

Does high-concentration PRP decrease pain and improve function more in the short term than saline injection (placebo) for thumb-base osteoarthritis?

### Hypotheses

High-concentration PRP injection will decrease osteoarthritis pain in the thumb baseHigh-concentration PRP injection will decrease pain and improve function more than saline (placebo) for osteoarthritis in the thumb base

## Methods

### Design

The design is a single-center randomized patient and assessor-blinded controlled trial. Figure 1 shows a flowchart of the study (Fig. 1), and details are listed in the SPIRIT figure (Fig. 2). The SPIRIT checklist is available as a supplement (S1). The study is conducted at the Department of Hand Surgery, Södersjukhuset, a hand trauma unit in Stockholm, with a catchment area of 2.8 million people.

**Fig. 1 Fig1:**
[figure not shown]
Flowchart of study

**Fig. 2 Fig2:**
[figure not shown]
SPIRIT figure

### Interventions

High-concentration PRP injection PRP injection (0.6–1 ml). Arthrex ACPmax systemSaline injection (0.6–1 ml)

All injections are administered under sterile conditions and radiological guidance on the day of randomization. Injections are performed from the dorsal, just radial, or ulnar of APL and EPB. To mimic the PRP procedure, a blood sample is taken from patients allocated to saline injection, and they must wait in the waiting area for the injection just as long as patients allocated to PRP. Patients wear a blindfold during injection. After the injections, patients do not receive any specific conservative treatment (orthoses, joint protection education). In bilateral thumb base osteoarthritis cases, the more symptomatic joint is injected and assessed.

### Inclusion criteria

The following are the inclusion criteria: osteoarthritis in the thumb base, radiological Eaton-Littler class 1–3 [22], clinical signs of thumb base osteoarthritis (pain at palpation of the CMC-1 joint and pain during the provocation test).

### Exclusion criteria

The following are the exclusion criteria: rheumatoid arthritis diagnosis, ongoing infection in the hand or wrist, history of gout or pseudogout in the hand, inability to co-operate with the follow-up protocol (language difficulties, severe psychiatric disorder, cognitive impairment, drug addiction), chronic pain syndrome/centralized pain, intra-articular injection in the affected joint within 6 months prior to inclusion, Eaton-Littler class 4 (defined as symptomatic STT joint osteoarthritis).

### Outcome

The primary outcome is as follows: change of pain on load (numerical rating scale (NRS) 0–100) in the thumb from before the first injection to 6 months after.

The secondary outcomes are as follows:Change in PROMs (Patient-Reported Outcome Measures) from pre-injection to 3, 6, and 12 months, including Patient-Rated Wrist/Hand Evaluation (PRWHE) score [23], Nelson score [24], and HQ-8 score [25]Objective physical variables: key pinch and three-finger pinch strength measured by using the Saehan Medical® mechanical pinch gauges SH5010 (the mean value of three consecutive measurements is used), radial and palmar abduction of the first metacarpal [26], thumb opposition [27] (Kapandji score). All measurements are performed according to the manual for measuring motion and strength in the Swedish national quality registry HAKIR [26]Time for the patient to experience the need for an intervention in the form of renewed injection, steroid injection, or surgery within 1 year after injection. Any adverse events, complications, and failures (defined as lack of improvement or deterioration of pain) during the study period will be recorded

### Sample size

To show a difference of 20 points (out of 100), representing the minimal clinical difference [28], in pain on load NRS score between PRP and saline injection (SD 30) (3) after 6 months, 37 patients are required in each treatment arm. The power will be 80% (*p* < 0.05). To account for non-parametric outcomes and loss to follow-up, we aim to include 90 patients in total, 45 in each treatment arm.

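### The sample size is worded for a 6-month pain score with SD 30, but the primary outcome is change from baseline with no stated baseline adjustment, so its power may rest on an unstated correlation

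*Protocol article*

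**What the plan says.** The Outcome section defines the primary outcome as "change of pain on load (numerical rating scale (NRS) 0–100) in the thumb from before the first injection to 6 months after". The Abstract words it as a level at one time: "The primary outcome measure is pain on load (numerical rating scale) at 6 months". The Sample size section also uses the language of a score at a time point, planning for a 20-point difference "in pain on load NRS score between PRP and saline injection (SD 30) (3) after 6 months, 37 patients are required" per arm. Power is given as 80% at p < 0.05. The number is then raised to 45 per arm (90 in total) to allow for non-parametric outcomes and loss to follow-up.

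The Statistical analyses section assigns Wilcoxon tests and chi-square tests to non-parametric data, including change in PROMs. It also names generalized estimating equations adjusted for pain catastrophizing, gender and Eaton class. Baseline pain on load is not in that list. No baseline SD, no SD of change and no baseline-to-6-month correlation is given anywhere in the article.

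**The concern.** A score at 6 months and a change from baseline have the same expected between-arm difference under randomization, so the 20-point target serves both. Their SDs generally differ. The SD of change exceeds the SD of the score when the two visits are weakly correlated and falls below it when they are strongly correlated. The Sample size section attaches its SD to wording that reads as a score, while the outcome to be tested is a change.

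An analysis adjusted for baseline would largely remove the dependence on that correlation. The unadjusted comparison of change does not, and the GEE as described does not list the one covariate that would. At stake is whether the stated power applies to the primary outcome as defined. A shortfall would make a null result harder to interpret, and the Discussion intends to read a null result as showing that use of PRP for this condition is not justified.

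**Working it through.** **Inputs from the article.** Difference 20, SD 30, alpha 0.05, power 80%, 37 per arm required, 45 per arm enrolled (Sample size). Sidedness is not stated. Two-sided is taken, because the one-sided normal formula gives 28 per arm, not 37.

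**Reproducing the plan's figure.** A two-sided two-sample t-test with standardized difference 20/30 = 0.667 needs 36.3 per arm, rounded up to 37. Power at 37 is 80.8%. The arithmetic is correct for a variable with SD 30.

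**Reading A: 30 is the SD of change.** The calculation then already describes the primary outcome, and the 80% stands.

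**Reading B: 30 is the SD of the score at both visits** (assumed, as is r). Then

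SD of change = sqrt(30² + 30² − 2·r·30·30) = 30·sqrt(2(1 − r)).

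At r = 0.3 this is 30·sqrt(1.4) = 35.5. Rank-sum power is taken as t-test power with n multiplied by 3/π (0.955, the efficiency under a normal shift). Simulation with 20,000 runs agreed to within about 1 percentage point.

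| r | SD of change | t-test, 37 per arm | rank-sum, 37 per arm | rank-sum, 45 per arm, no loss |
|---|---|---|---|---|
| 0.2 | 37.9 | 61% | 59% | 68% |
| 0.3 | 35.5 | 67% | 65% | 73% |
| 0.4 | 32.9 | 73% | 71% | 79.6% |
| 0.5 | 30.0 | 81% | 79% | 86% |
| 0.6 | 26.8 | 89% | 87% | 93% |

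**Correlation at which power reaches 80% under reading B.**

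- 37 per arm: 0.49 by t-test, 0.51 by rank-sum.
- About 40.5 per arm (45 less 10%), rank-sum: 0.47.
- 45 per arm, rank-sum, no loss: 0.41.
- If the baseline SD were 20 and the 6-month SD 30, rank-sum: 0.35 at 37 per arm and 0.19 at 45.

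**Cost of the rank-sum test itself.** At SD 30 it needs 36.3/0.955 = 38.02, rounded up to 39 per arm instead of 37. Enrolling 45 covers 39 with loss of up to 1 − 39/45 = 13.3%.

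**Adjusting for baseline instead.** With baseline pain as a covariate, the residual SD is 30·sqrt(1 − r²), which never exceeds 30. On the t-test basis, power at 37 per arm is 81% at r = 0 (SD 30), 84% at r = 0.3 (SD 28.6) and 90% at r = 0.5 (SD 26.0). Under reading A adjustment does no harm either: the least-squares coefficient for baseline minimizes the residual variance, and simple change is the special case where that coefficient is fixed at 1. The price is one degree of freedom.

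**The case against.** The strongest reply is that nothing is miscalculated. The figure of 37 reproduces, the SD comes from a cited source, and it may well be the SD of change. The article also raises the number to 45 per arm for non-parametric outcomes, and the Discussion says the increase takes account of the uncertainty and expected variance of PROMs. Nor does the article make an unadjusted rank-sum test the sole primary analysis, since an adjusted GEE is also named.

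Most of this stands. The rank-sum penalty is about two patients per arm and the increase to 45 covers it, so it is no part of the defect. The article does not fix the SD's meaning, so a loss of power is possible but not shown.

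A reader might go further and infer that the stated 80% holds only if r is at least 0.5. The document does not support that as a general condition. It needs three things the article does not say: that 30 is the SD of the score, that the baseline SD is also 30, and that exactly 37 per arm are analysed. Drop the first and no condition on r applies. Drop either of the others and the threshold moves, to 0.35 with a baseline SD of 20 (rank-sum, 37 per arm) or to about 0.41 with all 45 analysed.

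What the reply does not remove is the mismatch in wording between Outcome and Sample size, or the absence of baseline pain from the listed covariates. The allowance for PROM variance is stated without a figure, and under reading B with no loss it is not enough at r = 0.3.

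**Conclusion.** The point holds in a conditional form. The planning figure is worded for a 6-month score, the primary outcome is a change, and the SD is tied to neither. If 30 is the SD of change, 80% power stands. If it is the SD of the score at both visits, power for unadjusted change ranges from 67% at r = 0.3 to 81% at r = 0.5 with 37 per arm by t-test. With 45 per arm and no loss it is 73% at r = 0.3 and just under 80% at r = 0.4 by rank-sum. These figures rest on an assumed r, equal SDs at the two visits, two-sided alpha 0.05 and a normal shift.

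This is an avoidable dependence on an unstated quantity. It is not an arithmetic error and not a demonstrated shortfall. It deserves correction because an analysis that removes it is available from data already being collected.

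**What to change.** 1. Statistical analyses: make the primary between-arm comparison one of 6-month pain on load adjusted for baseline pain on load, for example by adding baseline pain to the listed GEE covariates. Adjusted for baseline in a linear model, change and 6-month score give the same estimated treatment effect, so the outcome can still be reported as change.
2. Sample size: state whether 30 is the SD of the score or of the change, and give the power for the adjusted analysis. If it is the score SD, use 30·sqrt(1 − r²) with the assumed r shown.
3. Reconcile the wording of the primary outcome across the Abstract, Outcome and Sample size sections.
4. If unadjusted change is kept as the primary analysis, state that 80% power at 37 per arm requires an SD of change of about 30 or less.

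Cost: revised wording in these sections and a dated amendment. Enrolment stays at 90, and no new measurement is needed because the PROM questionnaires are already completed at baseline. Recruitment began in January 2024 and treatment is revealed to each patient at 6 months, so the amendment should be dated before any outcome data are compared by arm. Trial status expects data ready for analysis in autumn 2026.
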